### Data analyses

Quantitative data analysis will be conducted using SPSS version 28. Univariate analysis presenting the frequencies and percentages for categorical variables and the means and standard deviation (SD) for the continuous variables will be performed. For the bivariate analysis, t-tests and ANOVA or their nonparametric analogs (based on normality) will be conducted for within and between group associations with a *p*-value set at <0.05. For the qualitative data analysis, audio recordings obtained during data collection will be transcribed verbatim by the research team and will be analyzed by content analysis. Data will be analyzed using Nvivo12. Responses will be coded into themes and sub-themes, ensuring data saturation when no new information is discovered in data analysis. Comparison, mapping, and verification of conclusions will be conducted and arranged according to the study objectives. Prominent quotes from the participants will be selected and cited within the report.

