### Sample size estimation

For the feasibility of pilot studies, research has shown that a sample size consisting of 30 participants in a group is sufficient (44, 45). Based on this evidence, we plan to recruit a minimum of 10 and a maximum of 20 nurses and community health workers in each group per study site. Overall, the estimated sample size for the quantitative component of this pilot study across the three study sites is 120 (60 participants in the intervention group and 60 participants in the control group). The data obtained from this pilot program will be used to estimate a suitable sample size for our major study in the future (46). For the qualitative assessment, unstructured interviews will be conducted with the trainers. A full-group focus group discussion [>7 participants per group as defined by Cortini et al. (47)] will be conducted at each study site. For this study, we intend to engage 8–10 participants per site.

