### Participants

For each study site, 40 participants (20 interventions and 20 controls) will be selected from a minimum of 4 PHCs. Participant selection will be by cluster sampling in each study site. In order to prevent cross-contamination among the participants, those in the intervention and control groups will be selected from different centers. Eligible participants will be 18 years and older, who speak and respond to questions in English, are employed full-time as a Nurse or CHW at the selected PHCs, have had no previous exposure to oral health training, and be willing to participate in the study. Participants with previous exposure to oral health training and those who cannot commit to the entire duration of the training will be excluded from the study.

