### Participant recruitment

The permission to conduct the study was sought, and relevant approvals were obtained from the Permanent Secretary (PS) of the State Primary Boards, Permanent Secretaries of State Health Districts, Director of Nursing Services and the Director of Community Services. Nurses who are in the dental and maxillofacial unit and/or nurses who have assisted with Smile Train education and surgeries were excluded. The nominal rolls of nurses and community health workers in the State Health Districts served as the sampling frame, and five nurses and five community health workers who met the selection criteria were selected from each district by simple random sampling (balloting). To avoid contamination, participants from Health districts who were from more distant locations were selected for the control group, while the participants from locations closer to the training center were selected for the intervention group. Following the IRB approval from the Ethics Committee of the participating centers, each recruited participant signed a written consent before active recruitment into the study.

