### Intervention and control

The intervention and control groups will consist of participants selected by a non-random process but with comparable characteristics. Across the three study sites, a total of 60 PHC workers (20 Nurses and CHWs at each site) will be assigned to the intervention group, and a corresponding number of participants will constitute the control group. Participants in the control group will receive a one-off conventional oral health education session consisting of a lecture on oral health, tooth brushing, and diet and oral hygiene demonstration using dental models. The intervention group will be exposed to the week-long pilot training on oral health education delivered by designated trainers (see Table 2). They will also participate in group activities such as oral exams and activity sheets. Each module is expected to last for approximately 4 h. Participants in the intervention group (those who will be trained) will be compared to the control group at each study site. Before the training begins, each participant will be administered a pre-intervention questionnaire to evaluate their oral health knowledge at baseline. The assessment will be repeated immediately after training and after 3 months. These evaluations not only serve as a means of monitoring training impact but also allow participants to observe how they improve throughout the training.

**Table 2 tab2:** Program and module delivery for the five-day training.

Day	Module
Day 1	Pre-intervention test Introduction to oral health
Day 2	Introduction to oral diseases and conditions
Day 3	Techniques in oral health promotion and oral disease prevention
Day 4	School and community-based oral health promotion
Day 5	MCOH Post-intervention test Facilitator assessment of participants capability to provide oral health education.

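### Recruitment is built by state and by cadre, but the stated bivariate between-group tests use neither, and the article does not say how the three sites are combined

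*Protocol article*

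**What the plan says.** The sample is structured by two factors.

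- **State.** Under Participants, at each site "40 participants (20 interventions and 20 controls) will be selected from a minimum of 4 PHCs". Under Sample size estimation, "the estimated sample size for the quantitative component of this pilot study across the three study sites is 120", split 60 and 60. The same section also allows a range: "we plan to recruit a minimum of 10 and a maximum of 20 nurses and community health workers in each group per study site".
- **Cadre.** Under Participant recruitment, "five nurses and five community health workers who met the selection criteria were selected from each district by simple random sampling". Districts nearer the training center went to the intervention group and more distant ones to control.

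On analysis, two sections bear on the between-group comparison.

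- Data analyses: "For the bivariate analysis, t-tests and ANOVA or their nonparametric analogs (based on normality) will be conducted for within and between group associations", with the p-"value set at <0.05". No stratum or covariate is named.
- Intervention and control: "Participants in the intervention group (those who will be trained) will be compared to the control group at each study site".

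The Null hypothesis section poses a single contrast of trained participants with controls. No section says whether or how the three site comparisons become one result.

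**The concern.** A t-test or its rank analog on group alone leaves differences between states and between nurses and CHWs in the error term, although the design has balanced them across groups. That loses precision. If the balance fails, part of a state difference can enter the estimated training effect.

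The point matters most for the picture test and logged referrals. The article describes no baseline value for these, so state and cadre are the known design variables left to adjust for. It also matters later, because the pilot data are to size the main study. An SD that still contains state and cadre variation would be larger than a stratified main study needs.

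**Working it through.** **1. The plan's own figure.** 3 sites × 2 groups × 20 = 120, as stated. The permitted minimum is 3 × 2 × 10 = 60. At 5 + 5 = 10 per district, a group of 20 needs 2 districts, so there are 2 × 2 × 3 = 12 districts. If the quota is met, each group has 10 nurses and 10 CHWs per site. The article gives no effect size, SD or power, so no power statement can be reproduced.

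**2. Precision lost in a 60 versus 60 comparison.** Assumptions: two-sided 0.05 (sidedness is not stated), independent participants, and d = 0.516, the effect that gives 80% unadjusted power. If state and cadre explain a share R² of the variance, the adjusted standardised effect is d/√(1 − R²).

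| R² (assumed) | 0 | 5% | 10% | 12% | 15% | 20% | 25% |
|---|---|---|---|---|---|---|---|
| Power | 80% | 82% | 84% | 85% | 86% | 88% | 90% |

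**3. What would produce such R².** Take a cadre gap c and state means −g, 0, +g, in within-stratum SDs. Then v = c²/4 + 2g²/3 and R² = v/(1 + v).

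- c = 0.5, g = 0.5: v = 0.0625 + 0.1667 = 0.229, R² = 19%.
- c = 0.5, g = 0.3: v = 0.0625 + 0.06 = 0.1225, R² = 11%.
- c = 0.5 alone: v = 0.0625, R² = 6%, a gain of about 2 points.

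**4. Error rate with equal strata and no clustering.** The unadjusted test is conservative. Its true size is about 2[1 − Φ(1.96/√(1 − R²))], which is 4.4% at R² = 5% and 2.8% at R² = 20%. Simulation of the 0.5/0.5 case gives about 3%.

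**5. Site-mix bias.** Bias = Σ over sites of (intervention share − control share) × site mean.

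- Planned 20/20/20 in both groups: 0.
- One group with 15 instead of 20 at one site that differs from the other two by D: 15/55 − 20/60 = −0.061, so 0.03 SD in size at D = 0.5.
- Largest under the 10 to 20 range with one differing site (10/10/20 versus 20/20/10): 20/40 − 10/50 = 0.30, so 0.15 SD at D = 0.5.
- Opposite fills of 20/15/10 and 10/15/20 (45 per group), states in equal steps g: size 20g/45, so 0.13 SD at g = 0.3 and 0.22 SD at g = 0.5. Simulated type I error is about 9% and 14%.

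**6. Strata without district.** Simulated with no training effect, 2 districts per group per state, 10 people per district, c = g = 0.5, and an assumed district intraclass correlation (ICC):

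| District ICC | Plain t-test | Group + state + cadre, district ignored |
|---|---|---|
| 0.02 | about 5% | about 7 to 8% |
| 0.05 | about 7% | about 11% |
| 0.10 | about 12% | about 16% |

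An analysis of district means adjusted for state held about 5% throughout.

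**7. Separate tests by site.** At 20 per group and d = 0.516, each site's test has about 36% power.

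**The case against.** **Pooling is not stated.** A reader might infer that the plan prescribes one pooled test as its headline result. The documents do not say so. The Intervention and control section says groups are compared at each site, and a within-site test has no state-mix bias. This stands. What is left is that the hypothesis and sample size describe one comparison, the site-level wording describes three, and Data analyses does not connect them.

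**Bias is not built in.** A reader might also infer that state differences will distort the training effect. With a cap of 20 per group per site, a total of 60 per group can only be 20/20/20, and site-mix bias is then exactly zero. Meeting the cadre quota likewise removes cadre bias. The larger bias figures need opposite shortfalls in the two groups, and a plausible single shortfall gives little. This stands too. The risk depends on recruitment within the permitted range and on losses by three months.

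**This is a pilot without a power target.** The 80% anchor and every R² are assumptions, and for knowledge scores the gain shrinks once the baseline score is in the model. That limits the weight of the point but does not remove it.

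**Adjustment alone can make matters worse.** Step 6 confirms this, so the remedy has to carry district.

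**An unseen analysis plan may name the strata.** It may. But the article does not leave the test open: it names a bivariate method that does not match the sampling it describes.

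**Conclusion.** The point holds as a mismatch between sampling and stated analysis, together with two sections that need reconciling on how sites are combined. If the comparison is 60 versus 60, omitting state and cadre costs about 2 to 10 points of power for an R² of 5% to 25%. That range is assumed and treats participants as independent. With equal strata and no clustering the plain test errs on the cautious side, so the documents do not support a claim that omitting the strata by itself produces false positives. Site-mix bias is conditional on unequal fills or losses. Nor would stratum terms remove the confounding from giving training to near districts and control to distant ones, which the Discussion discloses only in general terms as possible selection bias.

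**What to change.** Reconcile Intervention and control with Data analyses by stating one between-group model for each participant-level outcome:

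- Group, state (three levels) and cadre (nurse or CHW) as fixed effects.
- District, the unit of selection and assignment under Participant recruitment, in the error term. Use either a random effect with small-sample degrees of freedom or a state-adjusted analysis of district means. Cadre cancels from the district means when the five-and-five quota is met.
- For logged referrals, a count model with group and state. Add cadre only if referrals are logged per worker, since it is undefined if they are counted per center. The same clustering concern applies.
- Report the group estimate with its 95% CI.
- Size the main study from the residual SD together with the between-district variance, not from the residual SD alone.

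The cost is a few sentences, and state, cadre and district are known from recruitment. State and cadre take 3 degrees of freedom out of 118. The real price is the district term: a district-mean analysis has 12 − 4 = 8 degrees of freedom, so intervals will be wider, as the number of independent units warrants.

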In the present day, Nigerian PHCs rarely or sparingly provide oral health care (15). The direct connection of the PHCs to communities and individuals makes it the ideal platform for reaching the “*last mile*” population, primarily found in rural and underserved areas (7, 15, 17). PHC staff, including community health workers and nurses, are trusted members of the community. Exposing them to oral health education would provide them with a channel to amplify accurate health information within their communities while improving awareness about the burden of oral diseases. This could help promote health and oral health-seeking behaviors as well as prioritization of interventions for prevention and management. It is thus essential to adequately educate PHC workers before enrolling them on oral health promotion efforts, since research has revealed a lack of exposure to oral health education via their traditional training (18). Furthermore, successes from community-driven oral health promotion practices in Africa have been reported in countries such as Burkina Faso, Kenya, Cameroun, and Gambia (7). However, the absence of a model upon which oral health promotion can be built is a significant barrier to program implementation (18). This is because the application of sound and evidence-based models and theories provide a foundation for program planners to design, implement and evaluate effective health promotion programs (19). One such approach is Intervention Mapping (IM). IM is a planning framework useful for interventions targeted at behavioral change (20). It provides a template for the systematic planning, development, and evaluation of health promotion interventions (21, 22). IM has been characterized by three perspectives; the use of empirical evidence and theories, an ecological approach and stakeholder participation (20, 21), the outcome of which is more effective interventions (22). Despite its use in developing and implementing health interventions across the globe, there is a paucity of information on its use in health promotion planning in Nigeria, particularly in relation to oral health promotion.

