#### Null hypothesis

No measurable difference will be observed in the post-intervention knowledge scores and referral practices as it relates to oral health between participants with access to the 5-day training workshop vs. the control group.

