### Program assessment/evaluation

The assessment of the study outcome will be performed using a quantitative and a qualitative approach. Quantitative assessment will be conducted using questionnaires administered by the designated trainers, and the data will be fed into the Qualtrics software for data management. Before the training commences, all participants will take the pre-intervention test that measures their initial knowledge of oral health. The questions will be co-developed by Dental Public Health (DPH) consultants and educators on the research team based on available evidence and will be assessed for face and content validity before deployment. The questionnaire will also be pre-tested among participants who would not be involved in the study. The control group will be immediately provided with the post-intervention evaluation after the one-day lecture. After the training, participants in the training group will be assessed using the post-test. The pre and post-test scores will be compared for participants in the treatment and control groups. Participant’s capability to screen and detect oral diseases will be assessed post-intervention using picture tests.

After 3 months, a follow-up evaluation will be conducted. The number of logged referrals from the PHCs to the dental centers for oral health conditions will also be assessed for 3 months post-training based on the information logged by these providers (see Logic Model-Table 1). In addition, 5% of patients who were referred to dental centers as entered in the logbooks will be contacted via phone calls to verify their final visit to the dental centers.

The qualitative assessment to assess the impact of the training, points of improvement and the practicability of incorporation of oral health promotion activities into maternal and child health visits will be conducted with select participants in the intervention group at the 3-month evaluation using Deliberative Focus group discussions. This approach to evaluation serves to enhance program feedback through participants’ experiences and opinions. Refresher training will be conducted accordingly in month three if necessary. Data collection will be from February to May 2024.

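### A normality check decides whether the referral count is tested by means or by ranks, so the quantity tested for that outcome depends on the data

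*Protocol article*

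**What the plan says.** The Data analyses section of the protocol article gives one rule for bivariate comparisons: "For the bivariate analysis, t-tests and ANOVA or their nonparametric analogs (based on normality) will be conducted for within and between group associations". The significance level is 0.05. The section does not name the normality check and makes no exception for counts. For description it plans that "the means and standard deviation (SD) for the continuous variables will be performed".

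The referral outcome is a count. Under Program assessment/evaluation, "The number of logged referrals from the PHCs to the dental centers for oral health conditions will also be assessed for 3 months post-training". The logic model (Table 1) lists patients referred per three months as an output and a rise in the number of referrals as a short-term outcome. The null hypothesis covers both outcomes: "No measurable difference will be observed in the post-intervention knowledge scores and referral practices as it relates to oral health". It is not worded in means.

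The article gives no expected mean, spread or shape for referrals. The nearest statement is in the Introduction: "In the present day, Nigerian PHCs rarely or sparingly provide oral health care".

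**The concern.** A t-test and a rank test answer different questions when the data are skewed. The t-test compares mean referrals, and so total volume. The Mann-Whitney test asks whether a worker drawn from one arm tends to log more than a worker drawn from the other. With many zeros and a few high referrers the two can disagree, even in direction. Under the printed rule the data decide which question is answered.

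Referral practice is named in the hypotheses, and Table 1 frames it as volume. Training that turns a few workers into active referrers and leaves the rest unchanged would raise both the mean and the dispersion in one arm only. A rank test handles that pattern badly. The Sample size estimation section also says the data will be used to size the major study. That calls for a mean or ratio with its uncertainty, and the planned rank p-value does not supply one.

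**Working it through.** **Inputs from the article.** The Sample size estimation section says that "the estimated sample size for the quantitative component of this pilot study across the three study sites is 120". This reproduces: 3 sites × 20 per group × 2 groups = 120, or 60 per arm. The same section says that "we plan to recruit a minimum of 10 and a maximum of 20 nurses and community health workers in each group per study site", so the minimum is 3 × 10 = 30 per arm. Alpha is 0.05, taken as two-sided.

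**Assumptions (the article gives no figures).** Referrals per worker are negative binomial with mean μ and dispersion k, so the variance is μ + μ²/k and the share of zeros is (k/(k+μ))^k. Smaller k means more skew. Workers are treated as independent, so clustering by PHC is ignored. The check is Shapiro-Wilk at 0.05 in each arm; if either arm fails, Mann-Whitney is used.

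**Step 1: how often the rule leads to the rank test.**
- k ≤ 1: 100% of data sets at 60 per arm, 99.9% to 100% at 30 per arm.
- k = 5, mean 5 to 20: 92% to 99% at 60 per arm, 60% to 75% at 30 per arm.
- Poisson, mean 10: 32% to 43% at 60 per arm.
- PHC as unit (about 6 per arm if the minimum of 4 PHCs per site is split evenly), k ≤ 1: 37% to 97%.

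The rank route is near certain only for strongly skewed worker-level counts. Otherwise the test can switch from one data set to the next.

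**Step 2: what the rank test sees.** It targets θ = P(X<Y) + ½P(X=Y), with X a control count and Y an intervention count; 0.5 means no difference. Take mean 2, k = 2 in control and mean 4, k = 0.3 in intervention. The share of zeros is (2/4)² = 25% in control and (0.3/4.3)^0.3 = 45% in intervention. Summing over the two distributions gives θ = 0.472. The mean has doubled, yet the rank test leans slightly the other way.

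**Step 3: rejection rates, simulated, 60 per arm.** The mean-ratio column is a log ratio of means with robust standard errors.

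| Mean, control → intervention | k, control / intervention | θ | Mann-Whitney | Mean ratio |
|---|---|---|---|---|
| 2 → 2 | 1 / 0.3 | 0.413 | about 40% | about 6% to 7% |
| 2 → 2 | 2 / 0.3 | 0.381 | about 65% | about 7% |
| 2 → 4 | 2 / 0.3 | 0.472 | about 10% | about 70% |
| 1 → 2 | 0.5 / 0.5 | 0.590 | about 45% | about 63% |
| 2 → 4 | 1 / 1 | 0.643 | 79% | 90% |
| 2 → 4 | 2 / 2 | 0.688 | 96% | 98% |
| 1 → 1 | 0.5 / 0.5 | 0.500 | about 5% | about 6% to 7% |

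At 30 per arm, the first three rows give about 22%, 36% to 40% and 7% for Mann-Whitney. The mean ratio has about 43% power in the third.

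**Step 4: hand check of the mean-ratio power.** The variance of the log ratio is (1/n)(1/μ₁ + 1/k₁ + 1/μ₂ + 1/k₂). For the third row: (0.5 + 0.5 + 0.25 + 3.333)/60 = 0.0764, so SE = 0.276. Then ln 2/0.276 = 2.51, and power = Φ(2.51 − 1.96) = 71%. For k = 1 in both arms: 2.75/60 = 0.0458, SE = 0.214, 0.693/0.214 = 3.24, power = Φ(1.28) = 90%. Both agree with the simulation.

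**Step 5: wider range, with Welch's t-test as the mean-based comparator, 60 per arm.** With equal means, the rank test rejected in 11% to 14% (k 2 against 1) up to 77% to 91% (k 2 against 0.3), and Welch in 4% to 8%. With a doubled mean and a more dispersed intervention arm, rank power was 7% to 25% and Welch power 49% to 83%.

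**The case against.** Several objections stand.

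- **The rank route is not certain.** A reader might infer that referrals must fail the check. The documents report no referral distribution and name no check. The Introduction's remark concerns present PHC care, not referrals logged after training. Step 1 shows the t-test is often kept under milder skew or with the PHC as unit.
- **Effect sizes would not be lost.** Means and SDs are planned, and they yield a difference or ratio of means and an SD for planning. What is missing is an interval that belongs to the planned test.
- **The severe failures need arms of very different shape.** With equal shape the rank test holds its size, and at k of 1 to 2 it has 79% to 96% power for a doubling from 2 to 4.
- **The null is not worded in means.** A rank rejection with equal means is therefore not strictly a false positive. It is still not evidence of more referrals, which is what Table 1 seeks.
- **No pre/post contrast is lost.** The section states no group-by-time term on the parametric side either, a rank test on change scores would keep the contrast, and logged referrals are described only after training.
- **No harm is shown for knowledge scores.** On assumed score distributions with a smaller group gap, Welch and Mann-Whitney rejected in 73% and 72% of data sets and agreed in 93%.
- **The count model has its own weakness.** Robust Poisson rejected a true null (mean 2, k = 0.3) in 7% at 60 per arm and 9% at 30, and in 13% to 17% with six PHCs per arm as units, where Mann-Whitney gave 2% to 4%. With assumed PHC clustering that is ignored, it rejected in 14% to 22% and Mann-Whitney in 10% to 17%.

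It can also be said that a condensed article leaves outcome-specific models to the analysis plan. That does not remove the point: the article does not leave the method open but states a rule, and the rule covers the referral count.

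**Conclusion.** The point holds in a limited form and is worth acting on. The printed rule lets the data choose the quantity tested for a named count outcome. If referrals are low and strongly skewed, the comparison would almost always be made on ranks. If the arms also differ in dispersion, that comparison can reject at equal means (about 40% to 65% in the main scenarios) or miss a doubling (about 10% power against about 70%). If the arms share a shape, the cost is a moderate loss of power, such as 79% against 90%.

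Every mean and dispersion here is assumed, workers are taken as the unit, and clustering is left out. The percentages show what the rule can do; they do not forecast this study. That the choice of test depends on the data follows from the text alone.

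**What to change.** Delete the condition on normality and state the method for each outcome type in advance.

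- **Referrals:** the ratio of mean referrals, intervention to control, with a 95% CI from a negative-binomial or Poisson model. Standard errors should account for PHC with a small-sample correction. State whether the worker or the PHC is the unit, and keep the rank test as a sensitivity analysis.
- **Knowledge and picture-test scores:** the same mean-difference analysis with a 95% CI at every occasion.

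The cost is a few sentences in the Data analyses section, with no new data. SPSS, already named, fits both count models; whether the installed version offers the small-sample correction should be checked. The drawback is that the count model remains mildly liberal with few PHCs or very high dispersion, so its interval should be read as exploratory. That suits a pilot meant to inform a larger study.

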### Study design

We will utilize a quasi-experimental design (QED) (pre-and post-with a nonequivalent control group) to assess the impact of a five-day pilot oral health education program on the knowledge level and referral practices of Nurses and Community Health Workers in PHCs in three States in Nigeria - (Lagos, Oyo and Kano). A three-month post-training evaluation will follow this. A pre-training evaluation will be conducted prior to the commencement of training, and a post-evaluation will be conducted immediately and 3 months after training. Furthermore, we have included a qualitative assessment via unstructured interviews with the program trainers to explore their experience delivering the training modules and interacting with participants. We will also conduct a focus group discussion (FGD) with the participants in the intervention group to have an in-depth understanding of their opinions, training impact and points of improvement at the 3-month post-training evaluation. Quasi-experiments are often conducted to assess the effectiveness of a treatment, such as educational intervention in field settings where random assignment is not feasible (40–42). This method remains a quick and convenient approach to evaluating a target group to which an intervention has been applied (43).

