
In this study, we will ensure that a consistent approach is taken to select participants within and across study sites, administer evaluation surveys and follow-up (59). Additionally, we will conduct a pre-intervention assessment (allowing for the baseline comparison of the treatment and control group), an immediate post-intervention assessment, and 3 months following the training to allow for consideration of learning or attitude decay (43). Before use, the pre and post-tests will be validated for accuracy in measuring the outcomes of interest in the study. Also, tests will be scored consistently by a non-biased grader blinded to the participants and not part of the team that designed or conducted the oral health training (43). Regarding the establishment of causality, given that the intervention- (oral health education) comes before the assessment of the outcome, associations identified in QEDs meet an essential causality requirement (60).

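### No baseline-adjusted group contrast is named for knowledge scores, although the groups are formed non-randomly by distance and every participant takes a pre-test

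*Protocol article*

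**What the plan says.** The Study design section sets the frame: "We will utilize a quasi-experimental design (QED) (pre-and post-with a nonequivalent control group"). Under Participant recruitment, allocation follows geography: "participants from Health districts who were from more distant locations were selected for the control group", and those nearer the training centre form the intervention group. The Intervention and control section adds: "The intervention and control groups will consist of participants selected by a non-random process but with comparable characteristics".

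The null hypothesis reads: "No measurable difference will be observed in the post-intervention knowledge scores and referral practices as it relates to oral health", comparing those given the workshop with controls. The alternate hypothesis mirrors it. Neither mentions change from baseline or adjustment for it.

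A baseline score exists for everyone: "Before the training begins, each participant will be administered a pre-intervention questionnaire to evaluate their oral health knowledge at baseline". The assessment is repeated immediately after training and at 3 months. The Discussion describes the pre-test as a "pre-intervention assessment (allowing for the baseline comparison of the treatment and control group").

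For the analysis, the Data analyses section states that "t-tests and ANOVA or their nonparametric analogs (based on normality) will be conducted for within and between group associations", at a 0.05 threshold. It introduces these as the bivariate analysis. The Discussion concedes that selection bias is possible and relies on an assumption that the groups are similar at baseline. It names no analytic remedy.

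**The concern.** Allocation by distance gives no reason to expect equal starting knowledge in the two groups. The pre-test is the one measured variable that speaks directly to this, and no stated between-group estimate uses it. If the main knowledge result is a plain comparison of post-training scores, part or all of any starting gap will be reported as a training effect. The bias can go either way: it inflates the effect if staff near the training centre start out knowing more, and masks it if they know less.

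Within-group pre/post tests do not fill the hole. Controls also receive an oral health lecture and demonstration, so both groups may improve. A significant change in one group and not in the other would not test the stated hypothesis.

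Precision is also at stake, because a pre-test that correlates with the post-test removes variance at no cost. The pilot's data are meant to size a later study, so a biased or needlessly imprecise group difference would carry forward.

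**Working it through.** **Inputs from the protocol article**
- 60 per group (Sample size estimation). Check: 3 sites × 20 per group × 2 groups = 120, which reproduces the stated total. No SD, effect size or power is given, so there is no power figure to reproduce.
- Threshold 0.05 (Data analyses); two-sided is assumed.

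**Assumptions (not in the documents)**
- Score SD = 1.
- Baseline gap g = 0.3 or 0.5 SD.
- Pre/post correlation r = 0.5 or 0.7.
- No clustering by centre or district.
- No true training effect.

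**Unadjusted post-score comparison**
- SE = √(2/60) = 0.183.
- Expected spurious difference = r × g if the gap regresses; = g if it is stable.
- False-positive rate = P(|Z + bias/SE| > 1.96).

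| g | r | bias r×g | bias/SE | error rate |
|---|---|---|---|---|
| 0.3 | 0.5 | 0.15 | 0.82 | 13.0% |
| 0.3 | 0.7 | 0.21 | 1.15 | 21.0% |
| 0.5 | 0.5 | 0.25 | 1.37 | 27.8% |
| 0.5 | 0.7 | 0.35 | 1.92 | 48.3% |

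With a stable gap the rates are 38% (g = 0.3) and 78% (g = 0.5). With a gap of 0.2 SD and r = 0.3 the rate is only 6%, so the result depends heavily on inputs that nobody yet knows.

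**Simulation check** (4,000 runs per case, gap regressing)

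| g | r | post-score t-test | adjusted for pre-test | mean spurious difference in change scores |
|---|---|---|---|---|
| 0.3 | 0.5 | 13.3% | 5.4% | −0.15 SD |
| 0.5 | 0.5 | 26.0% | 5.0% | −0.25 SD |
| 0.5 | 0.7 | 48.0% | 5.3% | −0.15 SD |

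The last column matches the formula g(r − 1). When the gap regresses, the change score is biased the other way.

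**If the gap is stable instead**
- The change score is unbiased, and adjustment for the pre-test leaves g(1 − r).
- At g = 0.3 and r = 0.5 that is 0.15 SD. The adjusted SE is 0.183 × √0.75 = 0.158, so bias/SE = 0.95 and the error rate is about 16%. The unadjusted comparison gives 38% in the same case.

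**Precision**
- Residual variance factor after adjustment = 1 − r²: 0.75 at r = 0.5 and 0.51 at r = 0.7, a cut of 25% and 49% from the unadjusted variance.
- With balanced baselines this is equivalent to 60/0.75 = 80 and 60/0.51 = 118 per group. Power for a 0.5 SD effect rises from 78% to 89% and 97%.
- A baseline gap takes back a little: the variance of the adjusted difference is multiplied by 1 + g²/4, which is 1.06 at g = 0.5.

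**The case against.** The strongest reply is that the text does not say that the between-group tests are run on post-training scores alone. The Program assessment/evaluation section says: "The pre and post-test scores will be compared for participants in the treatment and control groups". With two groups and three occasions, a t-test on change scores or a group-by-time ANOVA could fit those words, and an article may condense a fuller plan. A reader might therefore infer too much in saying that the plan discards the pre-test, or keeps it for within-group tests only. The documents do not state that. What stands is that no such estimate is named, the tests are labelled bivariate, and both hypotheses are set on post-intervention scores. The working shows that the choice between the possible readings matters.

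Second, several design features limit a gap. Previous oral health training is an exclusion, as is work in a dental unit. Nurses and community health workers are drawn in equal numbers per district, and the groups are equal in size at each site. Cadre and state are thus largely balanced, and adjusting for them does little for bias. This stands, but it does not remove what distance from the training centre may bring.

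Third, a reader might try to infer the likely gap from the number of centres and an intraclass correlation. The documents do not support this. They give a minimum number of centres per site, not the actual number, and no correlation. Such a figure would also include the ordinary sampling error of 0.183 SD, which the 5% test already allows for.

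Fourth, this is a pilot that admits possible selection bias and claims only associations. That lowers the severity. It does not make the unadjusted contrast the better choice, since formal hypotheses and a significance threshold are stated.

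**Conclusion.** The point holds as a fault in the specified method that should be fixed. As written, the plan pairs hypotheses on post-intervention scores with bivariate tests in groups formed by distance, and names no between-group estimate that uses the pre-test. Under the assumed gaps of 0.3 to 0.5 SD and correlations of 0.5 to 0.7, the 5% error rate would be about 13% to 48%, and 25% to 49% of the residual variance would be left in needlessly. These figures illustrate the risk; they do not estimate it, because the documents give neither the gap nor the correlation.

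Two stronger conclusions might be drawn, and neither is supported. One is that the knowledge result will be biased: no baseline data are reported, and the gap may be small. The other is that baseline adjustment restores the 5% rate. It does so only if the gap regresses as simulated; stable district differences leave g(1 − r), and unmeasured confounding by district is untouched. The point concerns the knowledge score, for which a pre-test exists; it does not extend to referral counts.

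**What to change.** In Data analyses, make the main between-group knowledge result a baseline-adjusted mean difference with 95% CI: post score on group and pre-test score, at the immediate and 3-month assessments. State and cadre may be added as design terms. Report the difference in change (group by time) alongside as a sensitivity analysis, because the two estimates can disagree in non-equivalent groups and a disagreement is itself informative. Reword both hypotheses to refer to baseline-adjusted post-intervention knowledge, and keep within-group tests descriptive. Add a sentence saying that the adjustment addresses only the measured baseline gap, not unmeasured differences between districts. If a change-score or group-by-time analysis was intended all along, say so explicitly.

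The cost is analysis wording only. No new data are needed, and SPSS version 28, already planned, can fit these models.
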